## Methods

In Western Cape and Limpopo, students in grade 8 (first year of high school) (age 13–14) are included in the study, in Dar es Salaam students in grades 5 and 6 (age 12–14) are recruited, and in Kampala students in Senior One – the first year of secondary school (age 12–15) – are invited to take part.

All four evaluations of interventions within the PREPARE project are based on cluster randomized designs [52] with schools as the unit of randomization. In Western Cape and Dar es Salaam there will be one pre-test and two post-tests (shortly after the delivery of the interventions and 12 months after baseline). In Kampala and Limpopo there will be one pre-test and one post-test data collections. All power calculations are based on power calculators where the effect of allocating clusters (school classes) instead of individual students is adjusted for, such as the University of Aberdeen Sample Size Power Calculator [53,54]. Intraclass correlations (ICCs) with schools as units of clustering are calculated based on data from previous data collections, and sample size estimates are based on information about ICCs as well as information about cluster size (number of students in relevant grades). Number of schools involved in the studies varies from 22 in Kampala to 40 in Western Cape. Stratification and matching techniques are applied differently in different sites, according to local circumstances.

During the pilot phases of the projects, a wide range of methods were applied, including personal interviews, focus group interviews and reviews of previous studies.

Questionnaires with pre-coded response categories are chosen as the most central approach to collecting data for the evaluation of interventions. A distinction is made between a set of core questions, which are common across sites, and special focus questions, which are unique to each site. Questionnaires are piloted in all sites. The core questions consist of those that are common for the two sites with the most comprehensive interventions (Western Cape and Dar es Salaam). In the Limpopo and Kampala sites, a smaller selection of core questions is included. Special focus questions are piloted only by the site in which they are going to be used. The minimum number of cases in each pilot data collection is set to 200. The language used during the development of questionnaire items is English. For versions in other languages than English (Swahili, Sepedi, Luganda, Afrikaans, and isiXhosa) translations are followed by re-translations and careful examination of discrepancies between original and retranslated versions.

All data collections will take place in schools and are carried out by trained interviewers from the research teams. Teachers will not be present in class during data collection. Each team will follow a standard procedure that is designed to provide all students with necessary background information, constitute a neutral and open setting, and avoid collaboration among students during the data collections. As advocated by Mathews and associates, active consent from parents has not been established as a norm for all sites [55]. Active consent from parents is required in three sites, Cape Town, Limpopo and Kampala. Passive consent is approved and will be practiced in Dar es Salaam. Active consent from students will be requested in all sites. In one site (Dar es Salaam) signed communal consents from head teachers and chairs of school parent committees will be also required.

### Western Cape

The Western Cape sample size was calculated for one of the primary trial outcomes, the annual incidence of sexual debut. We used estimates from the Western Cape SATZ study [11,12] to make assumptions about the prevalence of students reporting at baseline to be virgins (83%), the background incidence of sexual debut during the PREPARE follow-up period of 1 year (17%), the ICC (0.06) and attrition after one year (20%). We used the Hayes and Bennett formula [52] and calculated that to show a 50% relative reduction in incidence of sexual debut (17% in control schools and 8.5% in intervention schools) with 80% power for a 2-sided test with a significance level of 5%, we would need 19 schools in each arm, with 62 “virgins” at baseline in each school. We sampled 20 schools in each arm to allow for one school per arm to drop out of the study. An attrition of 20% is an optimistic estimate, in an environment where 55% of Grade 8 Western Cape students drop out before completing Grade 12. We made this assumption on the basis of our plans to improve on the SATZ attrition (26-28%) by taking the contact details of students and allocating resources to attrition management.

We assumed the Grade 12 pass rate at a school is an indication of the climate and functioning of the school and its potential ability to benefit from the PREPARE programme. Pass rate is correlated with the amount of school fees charged, indicating it is also a reflection of socioeconomic status. Using the database of public high schools in the Western Cape we excluded schools with Grade 12 pass rates below 40% (indicating their inability to deliver even on their core mandate) and above 97% (indicating well-resourced schools already able to offer students the types of interventions proposed by PREPARE). We also excluded schools in two of the 8 districts situated far from Western Cape, and schools with other HIV prevention trials. Then we stratified schools into two strata of equal size based on Grade 12 s pass rate.

To ensure allocation sequence concealment, a statistician at the Medical Research Council, who did not have any knowledge of the schools, allocated the schools within each stratum to intervention and control arms of the study. He ordered the schools randomly within each stratum and then used a random number generator to give each school a number. Within each stratum, he allocated the 10 schools with the lowest random number to the intervention arm, and the 10 with the highest to the control arm. Some of the schools in the sample have large numbers of Grade 8 students, and in such cases, we selected classes randomly to obtain a sample of at least 75 students.

The Western Cape instrument comprises a paper questionnaire in three languages, printed in full colour in an adolescent-friendly format resembling a “teen magazine” rather than an examination paper. It was piloted and tested during 2011.

A process evaluation will monitor the quality of implementation of the intervention and student uptake of, and participation in it. Process data will be collected through observations of intervention sessions, interviews with the intervention facilitators and focus groups with Grade 8 students.

### Dar es Salaam

The Dar es Salaam site power calculation was based on expected effects of the intervention on sexual debut. According to findings from the SATZ project, 4.8% of adolescents aged 12–14 years in Dar es Salaam were sexually active at baseline [12]. Our pilot results indicated a non-response proportion of 7%. We assumed that the baseline rate of sexual debut will be about the same in this study and that the PREPARE intervention would reduce the proportion of adolescents becoming sexually active by 2.0 percentage point (from 5.0% to 3.0%), corresponding to a 40.0% reduction. The ICC was set to 0.01. To achieve 80% power with a significance level of 0.05 in a two-sided test to detect that change, we would need 38 schools (19 schools in each arm) with 153 learners per school, totalling to 5814.

We listed all schools in the selected Kinondoni District (N = 138) and excluded schools without standard 5 and 6 (N = 6), schools that were privately owned (N = 3) and all special schools for disabled children (N = 8). Six schools served as pilot-schools. All the remaining schools (N = 115) were stratified in to two strata based on number of students and location (urban and semi-urban). All the schools were then matched by size and urban pairs and semi-urban pairs were generated. A total of 19 pairs were randomly selected. To ensure equal representation, numbers of urban and semi-urban pairs were selected proportional to the total number of pairs from each location. From each pair, one school was randomly allocated to the intervention group and the other to the control group.

In each intervention school, two streams from each of grades 5 and 6 were randomly selected to receive the intervention and participate in the evaluation. The same procedure was used in control schools in order to select streams that would be involved in the evaluation. In these streams, consenting students with passive parental consent are screened for eligibility for the evaluation including being able to read a standard statement and being in the age range 12–14 years.

The Dar es Salaam site questionnaire comprises a learner administered paper questionnaire in Swahili. Process evaluation will be conducted using observation of at least two of each classroom based, peer led and youth friendly clinic visit sessions; collection of narrative data to explore experiences and challenges during implementation from teachers, head-teachers, parents, health care providers and learners; and determination of percentage of scope covered from a random sample of learners workbooks to identify areas where content reflected in workbooks may have been missed.

To ensure data quality and participation, project staff will supervise the whole data collection process keeping track of the accrual rates over time. Repeated call back will be made to schools where large proportions of participants are missing during the initial visit. To evaluate intervention fidelity and quality a process evaluation procedure will be put in place to monitor the quality of implementation of the intervention, student attendance and understanding of the intervention. On-going process data will be collected during the implementation stage through observations of intervention sessions, exit interviews with students, peer educators, and teachers.

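### Dar es Salaam power calculation: the control-arm debut rate of 5.0% appears to come from a baseline prevalence (4.8%), with no debut incidence cited and no deduction for learners already active

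*Protocol article*

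**What the plan says.** All of the following is in the Protocol article, Methods.

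- **Outcome behind the sample size** (Dar es Salaam): "The Dar es Salaam site power calculation was based on expected effects of the intervention on sexual debut". Early sexual transition is a primary objective at this site (Study objectives).
- **Only empirical rate given:** "4.8% of adolescents aged 12–14 years in Dar es Salaam were sexually active at baseline", credited to SATZ.
- **Link to the new study:** "We assumed that the baseline rate of sexual debut will be about the same in this study".
- **Planned effect:** the intervention "would reduce the proportion of adolescents becoming sexually active by 2.0 percentage point (from 5.0% to 3.0%), corresponding to a 40.0% reduction".
- **Other inputs:** "The ICC was set to 0.01"; 7% non-response in the pilot; 80% power at a two-sided 5% level. The result is 19 schools per arm with 153 learners each, 5814 in total.
- **Follow-up:** the second post-test is 12 months after baseline (opening part of Methods).
- **Western Cape:** this site also uses SATZ estimates but lists two inputs, 83% virgins at baseline and, separately, "the background incidence of sexual debut during the PREPARE follow-up period of 1 year (17"%). It then counts 62 virgins per school.

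**The concern.** The share of 12- to 14-year-olds already active at one survey has built up over all earlier years. The share becoming active is an incidence over at most 12 months among those not yet active. The Dar es Salaam text moves from the first to the second by calling the earlier figure a rate of debut. It offers no other source for the 5.0%.

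Reading 5.0% and 3.0% as prevalences does not help. Debut cannot be undone, so if about 4.8% are already active at baseline in both arms, the intervention arm cannot end at 3.0%.

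The control-arm event rate drives power for a primary outcome. If it has no basis as an incidence, neither has the stated 80%, and a null result on debut would be hard to interpret.

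**Working it through.** **Inputs.** From the Dar es Salaam text: p1 = 0.05, p2 = 0.03 (a 40% relative reduction), ICC 0.01, k = 19 schools per arm, m = 153, two-sided 5%, 80% power. Assumed, because the document gives no figure: a 12-month control incidence between 2% and 8%. Normal approximation; the pair-matching is not modelled.

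**Step 1: the plan's own figure.**

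- Design effect: 1 + (m − 1) × ICC = 1 + 152 × 0.01 = 2.52.
- Individually randomised size per arm: (1.960 + 0.842)² × [0.05 × 0.95 + 0.03 × 0.97] / 0.02² ≈ 1503. The pooled-variance version gives 1506.
- With clustering: 1506 × 2.52 ≈ 3795 per arm; 3795 / 153 = 24.8, so **25 schools per arm**, against the stated 19.
- Power of 19 × 153: effective size 2907 / 2.52 = 1153.6 per arm; standard error √[(0.0475 + 0.0291) / 1153.6] = 0.00815; 0.02 / 0.00815 − 1.96 = 0.494; power = Φ(0.494) ≈ **69%**.

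The stated 19 is therefore not reproduced. A one-sided 5% test (19.6 schools, power 79%) or an ICC of about 0.006 (power 80%) would come close, but the text states neither. This gap exists at the plan's own 5% versus 3%, so the choice of rate does not cause it.

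**Step 2: vary the control incidence p,** keeping the 40% relative reduction.

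Power = Φ( 0.4p / √{[p(1 − p) + 0.6p(1 − 0.6p)] × 2.52 / 2907} − 1.96 )

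| Assumed 12-month control incidence | Intervention arm | Power of 19 × 153 per arm | Schools per arm for 80% |
|---|---|---|---|
| 2% | 1.2% | 33% | 64 |
| 3% | 1.8% | 47% | 43 |
| 4% | 2.4% | 59% | 32 |
| 5% | 3.0% | 69% | 25 |
| 6% | 3.6% | 77% | 21 |
| 8% | 4.8% | 88% | 16 |

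The stated 80% is reached only at an incidence somewhere between 6% and 8%.

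**Step 3: the at-risk denominator.** If 4.8% of the 153 are already active, 153 × 0.952 ≈ 146 per school can have the event. At 5% versus 3% the design effect becomes 1 + 145 × 0.01 = 2.45, the effective size 19 × 146 / 2.45 ≈ 1132, and power about 68%. This is a loss of roughly one percentage point.

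**Step 4: the comparator.** Western Cape's 83% virgins means 17% already active at baseline, and its one-year incidence is also 17%. At that site the prevalence would have been numerically the same as the incidence.

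**The case against.** The strongest defence has four parts.

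- **The text does not say that 4.8% was entered as the control rate.** It gives 4.8% as background and then states an assumption of 5.0%. That is correct, and it is why the point is worded as what the calculation appears to do. But the two figures stand together, the linking sentence treats the SATZ figure as a rate of debut, and no other source is offered. The gap in the justification remains.
- **The 5% is not shown to be numerically wrong.** This stands in full. A reader might infer that 5% is too high and that the trial is therefore underpowered. The document does not support that: it contains no Dar es Salaam incidence, and the Western Cape figures show that the two quantities can coincide.
- **The shortfall from 80% is not due to the rate.** This also stands. A reader might set 47% or 69% against the stated 80% and blame the event rate for the whole gap. The fall from 80% to 69% occurs at the plan's own inputs; only movement away from 69%, in either direction, belongs to this point.
- **The denominator is a minor matter.** It costs about one point of power. Whether 153 already allows for the 7% non-response is not stated, so deducting it again could count it twice. The text says learners without saying whether those already active are among them.

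A reader might also infer that the outcome itself is wrongly defined. It is not: the text already names debut and becoming active, both new events. The exact at-risk analysis set is a detail that a condensed article may leave to the full protocol.

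**Conclusion.** The point holds in a limited form. The control-arm rate behind the Dar es Salaam sample size has no stated basis as an incidence; its only visible source is a baseline prevalence, and the article's own Western Cape section shows the two kept apart. The direction and size of any error are unknown.

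Across assumed incidences of 2% to 8%, the power of the 19 × 153 design runs from about 33% to 88%, around a reference of 69%. This rests on a constant 40% relative reduction, ICC 0.01, a two-sided 5% test, a normal approximation and no allowance for pair-matching. The failure of 19 schools per arm to follow from 5% versus 3% is a separate error, and should be corrected as such.

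**What to change.** - Replace the 5.0% with a 12-month debut incidence among learners not active at baseline. Use the SATZ Dar es Salaam comparison schools if they can supply one; otherwise state an explicit assumption with a range.
- Count about 146 at-risk learners per school (153 × 0.952), and say whether 153 is before or after the 7% non-response.
- Restate the power, or the detectable difference, of the 19-pair design on that basis. The pairs have already been selected, so the stated justification changes and the sample does not.
- In the same revision, correct the arithmetic so that the stated power follows from the stated test and ICC.

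The cost is one re-run of the calculation and a few sentences of text. Whether SATZ yields a usable 12-month incidence for this site is not confirmed in the document. The stated power is likely to become less favourable: at 5% it is already 69%, and it reaches 80% only if incidence is above about 6%.

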**Methods/design:**

A modified Intervention Mapping approach is used to develop all programmes. Cluster randomised controlled trials of programmes delivered to school students aged 12–14 will be conducted in each study site. Schools will be randomly allocated (after matching or stratification) to intervention and delayed intervention arms. Baseline surveys at each site are followed by interventions and then by one (Kampala and Limpopo) or two (Western Cape and Dar es Salaam) post-intervention data collections. Questionnaires include questions common for all sites and are partly based on a set of social cognition models previously applied to the study of HIV-preventive behaviours. Data from all sites will be merged in order to compare prevalence and associations across sites on core variables. Power is set to .80 or higher and significance level to .05 or lower in order to detect intervention effects. Intraclass correlations will be estimated from previous surveys carried out at each site.

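### Dar es Salaam: 19 schools per arm with 153 learners each give about 69% power under the stated inputs, not 80%; about 25 schools per arm would be needed

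*Protocol article*

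**What the plan says.** All the inputs are in the Dar es Salaam subsection of Methods. The intervention is assumed to reduce the proportion becoming sexually active "by 2.0 percentage point (from 5.0% to 3.0%), corresponding to a 40.0% reduction". The clustering assumption is "The ICC was set to 0.01". The aim is stated as "To achieve 80% power with a significance level of 0.05 in a two-sided test to detect that change", and the result as "we would need 38 schools (19 schools in each arm) with 153 learners per school, totalling to 5814". A 7% non-response figure from the pilot is mentioned, but the text does not say whether 153 is before or after it.

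Schools are the randomised unit, in matched pairs: "From each pair, one school was randomly allocated to the intervention group and the other to the control group". The opening of Methods says the ICC is a school-level quantity: "Intraclass correlations (ICCs) with schools as units of clustering are calculated based on data from previous data collections". The abstract says of the project as a whole: "Power is set to .80 or higher and significance level to .05 or lower in order to detect intervention effects".

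**The concern.** The article prints every input and also prints the answer, so the calculation can be repeated. An ICC of 0.01 looks small, but with 153 learners per school it multiplies the required sample by about two and a half. The printed total is less than twice the unclustered requirement.

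Early sexual transition is part of this site's primary objective (Study objectives), and debut is the only Dar es Salaam outcome with a printed power calculation. If the true power is well below 80%, a null result would be read against a sensitivity that the stated assumptions do not support.

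**Working it through.** **Inputs (Methods, Dar es Salaam).** p1 = 0.05, p2 = 0.03, ICC = 0.01, two-sided α = 0.05 (z = 1.96), power 80% (z = 0.8416), m = 153 per school, 19 schools per arm.

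**The plan's own total.** 38 × 153 = 5,814, or 2,907 per arm. This multiplication is correct.

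**Unclustered requirement per arm.**
(1.96 + 0.8416)² × (0.05 × 0.95 + 0.03 × 0.97) / 0.02² = 7.849 × 0.0766 / 0.0004 = 1,503. The pooled-variance form gives 1,506.

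**Design effect.** 1 + (153 − 1) × 0.01 = 2.52.

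**Schools needed.** 1,503 × 2.52 = 3,788 learners per arm; 3,788 / 153 = 24.8, so 25 per arm.

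**Power at 19 × 153.** The effective size is 2,907 / 2.52 = 1,154 per arm. The standard error is √(0.0766 / 1,154) = 0.00815, and 0.02 / 0.00815 = 2.454. Power = Φ(2.454 − 1.96) = 0.69. With 25 schools per arm it is 0.80.

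**Non-response.** If 153 is before the 7%, about 142 are analysed per school. The design effect is then 2.41, power is 0.68 and the requirement is 25.5 schools, so 26. If 153 is already net of it, power stays at 0.69.

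**Same method at the other sites.**

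| Site | Inputs | Computed per arm | Stated |
|---|---|---|---|
| Limpopo | effect 0.30, m 100, ICC 0.05 | 10.4 → 11 | 11 |
| Kampala | effect 0.35, m 50, ICC 0.06 | 10.1 → 11 | 11 |
| Western Cape | 17% vs 8.5%, m 62, ICC 0.06 | 17.9, plus 1 (Hayes–Bennett) = 18.9 → 19 | 19 |
| Dar es Salaam | 5% vs 3%, m 153, ICC 0.01 | 24.8 → 25 | 19 |

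**Other two-sided formulas, school clusters, ICC 0.01, m = 153.** Arcsine needs 24.4 schools per arm and the continuity-corrected form 26.4. Hayes–Bennett, with the between-school coefficient of variation k derived from the ICC and including the added 1, needs 23.5 (k = 0.436, taken at 5%) or 26.8 (k = 0.490, taken at 4%). None gives 19.

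**Small-sample check.** Replacing the normal by a t reference on 36 degrees of freedom gives 0.67. A beta-binomial simulation (20,000 runs) with an unpaired t-test on school proportions also gives 0.67, and 0.79 with 25 schools per arm.

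**What would give about 80% at 19 × 153.** An ICC of about 0.006 (design effect 1.91, power 0.80), or a one-sided 5% test (power 0.79). In the other direction, an ICC of 0.02 gives 0.49. With ICC 0.01 and a two-sided test, the difference detectable with 80% power is 5.0% against about 2.75%, a reduction of 2.25 / 5.0 = 45%.

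**The case against.** The strongest objection is that 19 may come from a different clustering unit. The opening of Methods describes the calculators as adjusting for allocation of school classes, and this site samples two streams in each of two grades. With school-by-grade clusters of 153 / 2 = 76.5, the design effect is 1 + 75.5 × 0.01 = 1.755. Inflating for 7% non-response gives 1,506 × 1.755 / 0.93 / 153 = 18.6, which rounds up to 19. This may explain the figure, but it is conjecture and would itself be an error: schools are randomised, and the same section puts the ICC at school level. It is a good reason to ask for the unit to be stated.

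A second objection is that pair matching on size and location may recover precision. Under a normal approximation, removing 30% of the between-school variance would give about 77% power, and removing 40% about 80%. The article gives no matching correlation and uses none in the calculation, so matching cannot support the printed 80%. If matching removed nothing, the paired analysis would lose degrees of freedom, and simulated power is about 65%. So 69% is what the stated inputs imply; the design's true power could differ.

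Third, loss to follow-up should not be counted as part of the error. A condensed article may leave it to the full protocol, and no loss rate is given for this site. Applying the Western Cape's assumed 20% loss and removing the 4.8% already active would leave about 108 learners per school and 62% power. That is an illustration only.

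Finally, the abstract sentence is a planning target for four sites. It needs amending as a consequence and is not a separate mistake.

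**Conclusion.** The concern holds. Under the article's own inputs, 19 schools of 153 per arm give about 69% power (about 68% with 142 analysed per school), roughly 11 percentage points below the stated 80%. Reaching 80% would take about 25 schools per arm (26 with 142 analysed). The type II error for the targeted reduction is about 31% instead of 20%.

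This assumes the school as the cluster, ICC 0.01, equal school sizes, a two-sided 5% test and no credit for matching. The first two and the sidedness are stated; the 153 per school is used as printed; and no matching gain enters the stated calculation. The gap is too large to come from rounding or choice of formula.

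**What to change.** Correct the sample-size paragraph for Dar es Salaam:

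- Keep 19 schools per arm. State that with a school-level ICC of 0.01 the two-sided power for 5.0% against 3.0% is about 69% (about 68% after 7% non-response), or that the design has 80% power for 5.0% against about 2.75%.
- If the ICC from the earlier project's data was really about 0.006, print that value and its source instead.
- State the unit of clustering used in the calculation, and whether 153 is before or after the 7% non-response.
- Credit a matching gain only if its assumed size and source are given.
- Amend the abstract's statement on power so that it no longer claims at least 80% for this site, unless the corrected inputs support it.

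The cost is a change of text. The article already reports the 19 pairs as selected and allocated, and no extra schools are needed. The stated power becomes less favourable unless a smaller ICC can be documented.
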